#### Appropriateness of assessments

BCVA assessment using ETDRS-like visual acuity testing charts is a standard assessment. The same applies for the fundus photography. Both assessments are clinical standard.

The ETDRS score is generally recognized as reliable, accurate, and relevant in BCVA assessment. Fundus photographs will be graded by an EPC to ensure a uniform, standardized evaluation and assessment. Grading is performed in accordance with the updated Classification of the Retina Society [20].

#### Endpoint committee

An EPC is established in order to evaluate the incidence of the primary endpoint in accordance with the classification of retinal detachment with proliferative vitreoretinopathy [21]. Some secondary endpoints will also be evaluated by the EPC. The EPC is composed of four independent and fully blinded members. The EPC members are experienced ophthalmologists and vitreo-retinal experts. The evaluation of the endpoint is performed on the basis of fundus photos that are taken at two different time points during the study. In case of any necessary re-operation related to previous retinal detachment or performed vitrectomy (i.e. retinal re-detachment) within 12 weeks after treatment, records of operation documentation (eCRF) will be reviewed. Furthermore, pre- and intra-operative fundus drawings of revision surgeries will be reviewed. The EPC will assess whether PVR development was the most likely reason for the additional revision surgery, whether the retina was attached prior to revision surgery, and whether revision surgery was categorized as serious. At least two members of the EPC will assess each single photo and documentation of revision surgery by applying the endpoints in regular meetings. The individual members will meet by appropriate means and together assess the provided data.

### Participant timeline

Each individual will be followed up for 3 months postoperatively (last study visit 12 weeks ± 10 days postoperatively).

#### Proposed overall timescale

Trial start: October 2016.

Projected trial end: October 2020.

Trial duration: 48 months.

Duration of each patient’s participation: 3 months.

### Sample size

#### Determination of trial size

Hoerster et al. reported a risk of 40% (8/20, 95% confidence interval (CI) 21.9–61.3%) for PVR grade CP 1 in a high-risk population (flare ≥15 pc/ms) [14]. Asaria et al. reported a risk of 26.4% (23/87, 95% CI 18.3–36.6) for PVR in the control group [7]. Therefore, we assume an incidence of PVR grade CP 1 of 35% in the control group. In the trial conducted by Asaria et al., the reduction of PVR events achieved about 50% (relative risk (RR): 0.48, 95% CI 0.25–0.92) [7]. Given a reduction of 33% (1/3) as clinically relevant (i.e. an RR of 2/3, or 0.6667), the incidence of PVR in the experimental group of our trial would be 23.33%. With a Pearson’s chi-squared test in a group-sequential study design with one interim analysis after half of the recruited patients and boundaries of O’Brien/Fleming, a two-sided type I error of 5%, and a power of 80%, 478 patients in total (239 in each group) are needed in order to show a significant result. Fisher’s exact test and Pearson’s chi-squared test with Yates’s continuity correction are too conservative and therefore have not been applied [22, 23].

Simulating the effect of the stratification by surgeon (assuming 24 surgeons with about 20 patients), an additional 5% of patients is needed to achieve the same power. This is in accordance with the results presented by Donner [24]. Therefore, 478/(1–0.05) = 504 patients need to be recruited, excluding any potential dropouts. It is expected that most of the patients are compliant and only a small number of patients (5%) will drop out (lost to follow-up). When the sample size for the dropouts is adjusted by using the formula given by Donner, then 504/(1–0.05)^2^ = 560 patients (280 per treatment arm) will be necessary for recruitment [24]. Sample size calculations were performed by using R, version 3.1.3, package gsDesign.

### Recruitment

Patient recruitment was not started before approval of the competent ethics committee (institutional review board, or IRB). IRB approval was obtained (IRB no. 16–192). At each trial site, the clinical trial does not commence prior to approval of the competent local ethics committee concerning the suitability of the trial site and the qualifications of the investigators. All 560 patients will be identified and recruited from emergency referrals at the trial sites.

### Assignment of interventions

Patients are randomly assigned to either the verum arm or placebo arm by using a 24-7 internet online randomization tool: TEN-ALEA (https://prod.tenalea.net/zkskoeln/dm/). In a previous study, results showed that the surgeon had a considerable influence on the outcome of surgery [25]; therefore, the randomization is stratified by the surgeon. The randomization list was generated by using permuted blocks of varying sizes and by a statistician independent of the trial team. In the rare case of unavailability of the service, a fax-based fallback procedure is to be used.

#### Blinding (masking)

Participants and all study team members are completely masked to the treatment allocation in order to avoid any bias regarding surgical management and postoperative treatment. Owing to identical appearance, the IMP components cannot be distinguished.

Unblinding at the request of the investigator should occur only in the event of an emergency or AE for which it is necessary to know the study treatment in order to determine an appropriate course of therapy for the subject. Unblinding is then carried out by the investigator, who has to inform the CTCC about the event of unblinding immediately (within 24 h at the latest).

For every suspected unexpected serious adverse reaction (SUSAR) occurring during the specified reporting period, treatment unblinding of the individual trial patient will be performed by CTCC before reporting the event to the ethics committee, the competent authority, and the data monitoring committee (DMC).

#### Withdrawal

Participants can withdraw at any time during the trial at their own or their legal representative’s request without providing a reason and without any personal disadvantage. A participant may also be withdrawn if, on the basis of the investigator’s judgment, continuation of the trial may be detrimental to the participant’s health. Other possible reasons for the investigator to discontinue or modify a patient’s trial participation include relevant intra- or post-surgical complications (i.e. endophthalmitis) or other uncontrolled ophthalmologic disorders not related to previously performed vitrectomy or to trial drug application. Reasons for all withdrawals will be recorded in the patient’s medical files and their CRFs. The analysis will include a listing of all patients who prematurely terminate the trial, indicating the reason for discontinuation and reporting the data available on patient characteristics as well as on prespecified outcome parameters.

### Data collection methods and data management

All clinical documentation (source data) and data arising from the trial are to be kept by the investigator/trial site and be available for review by the clinical research associate.

The eCRFs were designed and produced by the sponsor and data manager of the CTCC. The final version was approved by the sponsor. It will be the responsibility of the investigators to ensure the accuracy of all data entered on the CRFs. A delegation log at each trial site is used to identify all trial personnel with responsibilities for data collection and handling, including those who have access to the trial database.

Plausibility checks are run during data entry, thereby detecting discrepancies immediately. CTCC Data Management has conducted further checks for completeness and plausibility and will clarify any questions with the trial sites electronically via the trial software. These electronic queries have to be answered by the trial site without unreasonable delay.

The database is integrated into a general IT infrastructure and safety concept with a firewall and backup system. The data are backed up daily. After completion and cleaning of data, the database is locked and the data exported for statistical analysis.

Central quality control located at the data management facility provides regular reports to provide information to project management to identify trial sites that might benefit from additional quality assurance measures such as risk-adapted monitoring. Reports provide, for example, trial site–based information regarding quality of eCRF documentation, query response time, or missing data.

### Data protection

The provisions of data protection legislation are observed. It is ensured by the sponsor that all investigational materials and data will be pseudonymized in accordance with data protection legislation before scientific processing.

Trial subjects are informed that their pseudonymized data will be passed on in accordance with provisions for documentation and notification pursuant to § 12 and § 13 of the Good Clinical Practice (GCP) Regulations to the recipients described there. Subjects who do not agree that the information may be passed on in this way will not be enrolled in the trial.

The primary endpoint of the trial is the occurrence of PVR grade CP 1 within 12 weeks. The null hypothesis H_0_ is “the PVR grade CP 1 incidence is equal in both treatment groups (verum, placebo)”.  It will be tested by application of the Mantel–Haenszel test [27] accounting for the stratification by surgeon. The primary analysis is performed by using the mITT population. Missing values are assumed to be missing at random. For the primary analysis, a missing primary endpoint is considered a treatment failure. RRs and absolute risk reductions (with CIs and *P* values) will be given for the overall effect between the trial groups and within the strata.

Secondary endpoints will be evaluated by descriptive methods. Numerical data will be summarized by number of patients, mean, standard deviation, median, first quartile, third quartile, and minimum and maximum; categorical data will be summarized by number and percentage of patients. If *P* values are computed for the secondary parameters, no adjustment for multiplicity and interim analyses will be taken into account. Therefore, no confirmatory test decisions are possible with these *P* values. *P* values of not more than 0.05 (5%) are considered statistically significant.

For all primary and secondary parameters, descriptive statistics will be given overall and for each treatment group. Moreover, results of both stages and overall will be given.

The safety population includes all randomly assigned patients who received the initial surgery. Analysis is according to the treatment received. The analysis includes calculation and comparison of the rates of specified complications (see secondary endpoints) and SAEs as well as of severity and relationship to intervention and graphical display of the time course.

Furthermore, statistical methods are used to assess the quality of data and the homogeneity of intervention groups. Analyses will be carried out by using SAS version 9.3 (SAS Institute Inc., Cary, NC, USA) or IBM SPSS Statistics 23 or higher (IBM, Armonk, NY, USA).

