In two independent trials, we have recently identified high-risk patients for PVR by determining protein levels in the anterior chamber using non-invasive laser flare photometry [14, 15]. In eyes with flare values of at least 15 pc/ms (photon counts per millisecond), the odds for developing PVR re-detachment increased 16-fold. Sensitivity and specificity of flare measurements with a cutoff value of 15 pc/ms were 83.3% and 76% (area under the ROC curve of 0.85), respectively. Therefore, non-invasive laser flare photometry has been established as a possible tool for fast and precise estimation of high-risk patients for PVR re-detachments [15]. Conart et al. recently confirmed that preoperative aqueous flare seems to be a major predictive factor for PVR re-detachment [16].

The COCHRANE collaboration has recently reviewed two independent randomized controlled trials using 5-FU and LMWH to prevent PVR (Table 1). The first trial used 5-FU and LMWH in conventionally determined high-risk patients [7], the second trial in unselected patients [9]. High-risk patients benefited from 5-FU and LMWH whereas unselected patients did not [7, 9, 17]. Because results had been inconsistent, the COCHRANE collaboration recommended the use of 5-FU and LMWH in a randomized controlled trial in high-risk patients [17].

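### The primary test uses surgeon as its only baseline information; prespecified adjustment for continuous flare could add 0 to about 5 power points at little cost

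*Protocol article*

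**What the plan says.** Statistical methods in the protocol article takes equal PVR grade CP 1 incidence as the null hypothesis, to be "tested by application of the Mantel–Haenszel test [27] accounting for the stratification by surgeon". The P value of that test also drives the interim rule (stop at 0.0052 or less), and the stage P values are then combined by the inverse normal method. Under Assignment of interventions, "the randomization is stratified by the surgeon", on the ground that the surgeon influences outcome. Determination of trial size adds 5% for the surgeon strata. Randomisation, sample size and test therefore agree.

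Flare enters as an inclusion criterion (at least 15.0 pc/ms), so a numeric value exists for every randomised eye. On its predictive value, Background says: "In eyes with flare values of at least 15 pc/ms (photon counts per millisecond), the odds for developing PVR re-detachment increased 16-fold". It gives sensitivity and specificity for the "cutoff value of 15 pc/ms were 83.3% and 76% (area under the ROC curve of 0.85"), and reports a further study as confirming that "preoperative aqueous flare seems to be a major predictive factor for PVR re-detachment". No analysis described in the article uses how far above the threshold an eye lies.

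**The concern.** The reason given for stratifying by surgeon, that it affects outcome, applies to any strong baseline predictor. Flare is the predictor on which the trial's selection rests, yet the analysis uses it only as a yes/no entry gate. If flare stays prognostic above 15 pc/ms, a test that uses its value has more power with the same patients and measurements, and it corrects chance imbalance in flare, which randomisation by surgeon does not control.

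The extra power could be useful. The assumed control incidence of 35% lies between 8/20 (40%) and 23/87 (26.4%), and the design falls below 80% power towards the lower of these (step 2 under working).

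**Working it through.** **1. The plan's own figure.** Inputs from Determination of trial size: "we assume an incidence of PVR grade CP 1 of 35% in the control group"; with a relative risk of 2/3, "the incidence of PVR in the experimental group of our trial would be 23.33" per cent; "a two-sided type I error of 5%, and a power of 80%, 478 patients in total (239 in each group) are needed".

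- Pooled-variance formula: n per arm = (1.960·√(2p̄q̄) + 0.842·√(p₁q₁ + p₂q₂))² / (p₁ − p₂)², with p₁ = 0.35 and p₂ = 0.2333. Fixed-sample total: 474.2.
- Two-look O'Brien–Fleming boundaries: |z| ≥ 2.797 at the interim (P = 0.0052) and |z| ≥ 1.977 at the end. Inflation 1.0078: 474.2 × 1.0078 = 477.9, i.e. 478.
- 478/0.95 = 503.2, i.e. 504. 504/0.95² = 558.4, or 279.2 per arm, i.e. 280 per arm and 560 in all.

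The stated figures reproduce. By formula, group-sequential power is 82.1% at 504 evaluable patients, before any loss from the surgeon strata.

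**2. How firm that power is.** At a control rate of 23/87 = 0.264 and the same relative risk (0.176), a fixed-sample calculation with 252 per arm gives Φ[(0.0881·√252 − 1.960·0.5861)/0.5828] = Φ(0.43), about 67%.

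**3. What the flare evidence measures.** Sensitivity 83.3% and specificity 76% give an odds ratio of (0.833/0.167)/(0.24/0.76) = 15.8. The 16-fold figure is therefore the contrast across 15 pc/ms. Every trial eye is on one side of that line, so only variation above it can help.

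**4. Assumed strength above the cutoff.** The article gives none. As an upper guide, read the AUC of 0.85 as binormal: separation √2·Φ⁻¹(0.85) = 1.466, cutoff Φ⁻¹(0.76) = 0.706. Truncating both distributions there leaves an AUC of about 0.73, or an odds ratio of about 2.5 per SD. This model is only approximate: it implies a sensitivity of 77.6%, against the reported 83.3%. The assumed range is an odds ratio per SD of 1.0 to 2.5.

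**5. The adjusted test.** Fit logit P(y = 1) = a + b·log(flare) without a treatment term and take residuals r = y − p̂. Over surgeons k, with n₁ₖ verum and n₀ₖ placebo patients:

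- T = ΣₖΣ(verum)(r − r̄ₖ)
- V = Σₖ [n₁ₖn₀ₖ/(nₖ(nₖ − 1))]·Σ(r − r̄ₖ)²
- z = T/√V

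With y in place of r this is the Mantel–Haenszel statistic.

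**6. Simulation.** Two stages of 252 patients, 24 surgeons, allocation balanced within surgeon, surgeon-effect SD of 0.3 on the log-odds scale (assumed), the boundaries above, equal-weight inverse normal combination, 8,000 runs per row (Monte Carlo SE about 0.4 points).

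| OR per SD | AUC above cutoff | MH by surgeon | Residual test, surgeon + flare | MH by surgeon × flare halves |
|---|---|---|---|---|
| 1.0 | 0.50 | 81.9% | 81.8% | 77.8% |
| 1.5 | 0.61 | 82.9% | 83.9% | 79.5% |
| 2.0 | 0.68 | 82.0% | 85.0% | 79.9% |
| 2.5 | 0.73 | 82.6% | 87.3% | 81.7% |

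The residual test gains −0.1, 1.0, 3.0 and 4.7 points. Splitting the surgeon strata by flare loses 0.9 to 4.1 points.

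A second simulation (2,500 runs per setting) gave gains of 0.1, 1.4, 3.6 and 5.3 points at log-odds slopes of 0, 0.4, 0.7 and 0.9 per SD, which correspond to nearly the same odds ratios. A third, with 560 patients and 5% missing outcomes counted as failures, gave 0.2, 1.4 and 3.2 points at slopes of 0, 0.4 and 0.7. At a slope of 1.0, beyond the range in step 4, it gave 6.1.

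**7. Type I error.** Residual test: 5.2% in 2,000 runs (Mantel–Haenszel also 5.2%), and 4.5% against 4.4% in the second simulation. Ordinary logistic regression with a term for each surgeon gave 5.8% in one run, and 6.4% (Wald) and 6.6% (likelihood ratio) in another with 6,000 runs. It has only 252/24 = 10.5 patients per surgeon and stage.

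**The case against.** The strongest reply is that nothing here is wrong. The test follows the randomisation, the sample size allows for the surgeon strata, and the 80% target is met without flare. A supplementary adjusted analysis may also stand in an analysis plan that is not shown. All of this is right, so the point is an improvement and not a correction. It still bears on the article, because the confirmatory test itself is fixed there and an adjusted one would depart from it.

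A reader might infer that the 16-fold odds and the AUC of 0.85 prove that substantial power is being given away. The documents do not support that. Both figures concern the 15 pc/ms cutoff, whose contrast selection removes, and the evidence is on PVR re-detachment, not CP 1 or higher. The description of flare as a major predictor reports a cited study. If flare carries no information above the threshold, there is no gain.

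A further objection is that adjustment can do harm. That stands for two versions: extra flare strata lower power, and ordinary logistic regression with surgeon terms looks anti-conservative in such small strata. The residual test showed neither problem. It does need an amendment while the trial is recruiting, and it yields no effect estimate of its own, so test and interval could occasionally disagree.

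**Conclusion.** The point holds as a missed efficiency gain. The planned test is valid and adequately powered under its own assumptions, but it ignores a baseline value held for every randomised eye. Using continuous flare alongside surgeon would add between 0 and about 5 power points at 504 evaluable patients. For scale, going from 504 to 560 evaluable patients raises formula power from 82.1% to 85.8%, just under 4 points.

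The top of the range rests on a binormal reading of the reported AUC, on carrying evidence about re-detachment over to CP 1 or higher, and on log flare acting roughly linearly on the log-odds. The bottom needs only that flare is uninformative above 15 pc/ms, and there the cost in power is essentially nil. The gain was not simulated at lower control rates.

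**What to change.** Before anyone sees unblinded data, amend the interim and the primary-endpoint paragraphs of Statistical methods together:

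- In each stage, fit a logistic model of CP 1 or higher (missing counted as failure, as planned) on log baseline flare, without a treatment term.
- Apply the surgeon-stratified Mantel–Haenszel-type test to its residuals.
- Use the resulting stage P values in the 0.0052 interim rule and in the inverse normal combination.
- State that the surgeon strata are not subdivided by flare, and that ordinary (unconditional) logistic regression with surgeon indicator terms is not used for the confirmatory test.
- Report the relative risk and absolute risk reduction standardised over flare, and keep the unadjusted Mantel–Haenszel test as a sensitivity analysis.

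The cost is a protocol amendment and modest programming; no new patients or measurements are needed. The small downside is reliance on a one-covariate working model and an effect estimate computed separately from the test.

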Charteris et al. have reported a trial setting similar to that of Asaria et al., using a combination of 5-FU and LMWH but treating eyes with already-established PVR [11]. No significant differences in the number of potential complications due to the adjunct treatment (or the surgery or both) were found between treatment and control groups during the 12-month follow-up period [11]. Complications were reported for 98 patients of both groups, including glaucoma (0 versus 3 controls), hypotony (9 versus 7 controls), keratopathy (5 versus 2 controls), and cataract (21 versus 29 controls), indicating no drug-related AEs [11].

Wickham et al. again investigated the adjuvant effect of 5-FU (200 μg/mL) combined with LMWH (5 IU/mL) in comparison with placebo for RRD repair. No statistically significant difference between both groups with respect to retinal re-attachment rate (82.3% versus 86.8%) and visual acuity outcome (*P* = 0.072) could be detected. However, they reported that adjuvant treatment with 5-FU and LMWH of eyes with primary macula-on RRD led to a significant reduction in the final postoperative visual acuity in comparison with control patients (*P* = 0.0091) [9].

Until now, a major problem has been to identify patients at risk for PVR in order to limit potentially harmful chemotherapy to high-risk patients only and to improve statistical power. So far, high-risk patients for PVR have been determined in a complicated manner based on anamnestic risk factors such as diabetic retinopathy, accompanying uveitis, aphakia, or penetrating ocular trauma [7, 12, 13]. These existing methods for estimation are time-consuming and depend on observers’ judgment, and the area under the receiver operating characteristic (ROC) curve is low [7, 12, 13].

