#### Study visits and assessment schedule

Preoperatively, a screening visit (baseline) will be performed at the day of admission to the study center. Since a retinal detachment is an emergency, which is unpredictable and which should be treated as soon as possible, a scheduled screening cannot be performed in advance. Thus, the screening is carried out following the emergency admission to the trial centers. This will include a full ophthalmic examination with slit-lamp/indirect biomicroscopy, and a structured interview, which will include questions on coexisting ocular pathology and previous ophthalmic surgical procedures to confirm that all inclusion and exclusion criteria are satisfied, will be conducted by a member of the study group. Furthermore, urine pregnancy tests will be performed in women of childbearing age and potential. Clinical findings documented as part of the routine clinical care at the time of screening may be used to populate data in the baseline case report forms (CRFs) and used as part of the study data (if collected within 5 days prior to PPV including IMP application for retinal detachment repair). This information may be collected prior to informed consent for enrolment into the trial as no additional intervention is performed outside routine clinical care. Patients will be informed in detail about the purpose of the study as well as the risks and benefits. Written informed consent will be obtained prior to study-specific measures. Postoperative study visits will not differ from the routine schedule for vitreo-retinal procedures at the study site for the first 3 months. The first postoperative visit is between days 1 and 5, the second postoperative visit 6 weeks postoperatively (± 10 days), and the third 12 weeks postoperatively (± 10 days).

At each preoperative and postoperative study visit, again a full ophthalmic assessment will be completed and this will include slit lamp biomicroscopy (with indirect binocular ophthalmoscopy when required) and recording of parameters, including ETDRS visual acuity, Goldman applanation tonometry, anterior segment assessment, and retinal attachment status. Fundus drawing (at screening visit and surgery) will be performed to record preoperative and direct postoperative retinal status. Color fundus photography (nine-field or wide-angle) will be performed 6 and 12 weeks postoperatively for endpoint assessment (Fig. 2).

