### Adverse events and safety reporting

Safety reporting will adhere to the sponsor’s standard operating procedures. There is an external DMC, which has an agreed charter. It consists of two physicians and a statistician who are not involved in the conduct of the trial. The task of the DMC is to oversee the safety of the trial subjects in the clinical trial by periodically assessing the safety of the trial therapy. They will meet every six months or on an ad-hoc basis as required.

Expected AEs are development of PVR, retinal re-detachment, cataract, raised IOP, and further surgery. Unexpected AEs will include endophthalmitis, systemic illness, and ocular vascular occlusion.

Furthermore, an AE of special interest (AESI) has been defined in order to evaluate visual impairments due to potential toxic effects of the IMP at an early stage. The AESI will be handled as an SAE and has been defined as the lack of recovery of visual acuity (BCVA) to 0.3 log MAR/0.5 decimal or better and/or decrease of visual acuity (BCVA) to > 0.3 log MAR/< 0.5 decimal (compared with the last assessment of visual acuity prior to the most recent assessment) lasting more than 1 h during the postoperative course without morphological correlate in study eye that presented with primary rhegmatogenous retinal detachment with macula-on status prior to surgery.

All AEs are documented in the trial patient’s medical records and the eCRF, including date and time of onset and resolution, severity, causal relationship with IMP/study treatment, seriousness, and interruption or withdrawal of study treatment and other measures taken.

Regardless of whether a causal relationship between the AE and the IMP is suspected, trial patients who develop AEs must be monitored until all symptoms have subsided, pathological laboratory values have returned to pre-event levels, a plausible explanation is found for the AE, the trial patient has died, or the study has been terminated for the trial patient concerned. This information must be verified on the basis of the source data.

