Degree of PVR	PVR grade (CA 1–12, and/or CP 1–12)	- Value (yes/no) - Count (clock hours)	- Proportions - Means	- Within 6 weeks and 12 weeks
Best corrected visual acuity	ETDRS letters	- Count	- Means	- Within 6 weeks and 12 weeks
Retinal re-attachment after primary intervention	Retinal attachment in all 4 quadrants	- Value (yes/no)	- Proportions	- Within 6 weeks and 12 weeks
Number of retinal re-detachments	Number of retinal re-detachments if present, re-detachments due to PVR	- Count (>0) - Value (yes/no)	- Proportions	- Within 6 weeks and 12 weeks
Number and extent of surgical procedures to achieve retinal attachment	Number of procedures number of intraoperative procedures number of serious/ complex procedures	- Count (>0) - Value (yes/no)	- Proportions	- Within 12 weeks
Occurrence of at least one drug-related adverse event that affects the study eye	Drug-related adverse event that affects the study eye	- Count	- Proportions	- Within 12 weeks

Abbreviations: *CA* grade C anterior, *CP* grade C posterior, *ETDRS* Early Treatment Diabetic Retinopathy Study, *PVR* proliferative vitreoretinopathy

BSS equally packaged as the verum 5-FU and LMWH will serve as placebo to provide blinding of the trial. Usage of placebo is justifiable since no standard treatment for the prevention of PVR currently exists.

Primary analysis is according to mITT. Patients lost to follow-up within 12 weeks are counted as “events” if no information about PVR status can be obtained. This shall guard against overly optimistic results and minimize possible attrition bias. Throughout the trial period, all patients fulfilling main inclusion criteria are screened and documented. Monitoring of the trial is carried out in accordance with international GCP guidelines. Patients with other ophthalmologic disorders leading to blood-brain barrier breakdown and to additional risk for PVR are excluded to homogenize the sample.

In summary, according to the recommendation of the COCHRANE collaboration, the present trial uses intraoperative intravitreal 5-FU and LMWH as a prophylactic therapy in high-risk patients with primary RRD aiming to reduce the incidence of PVR in the group that receives the trial drug. Using laser flare photometry to determine high-risk patients for PVR, this trial will test the effectiveness of a simple treatment to prevent PVR (Additional file 1).

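### BCVA is fixed as an unadjusted descriptive summary by arm, with no estimated difference in macula-on eyes, where the protocol itself cites visual harm

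*Protocol article*

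**What the plan says.** All references are to the protocol article.

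- **Method.** Statistical methods: "Secondary endpoints will be evaluated by descriptive methods". It continues: "Numerical data will be summarized by number of patients, mean, standard deviation, median, first quartile, third quartile, and minimum and maximum".
- **Grouping.** "For all primary and secondary parameters, descriptive statistics will be given overall and for each treatment group". Results are also given by stage. Neither macula status nor surgeon is named as a grouping for secondary endpoints.
- **Tests.** "If *P* values are computed for the secondary parameters, no adjustment for multiplicity and interim analyses will be taken into account". Such P values are declared non-confirmatory, and no test is named for them.
- **BCVA metric.** Table 2 in the Discussion gives "ETDRS letters" as the measurement variable and means as the aggregation, at 6 and 12 weeks. Neither Table 2 nor the list of secondary endpoints defines BCVA as change from baseline.
- **Data at hand.** Study visits and assessment schedule requires, at every pre- and postoperative visit, "recording of parameters, including ETDRS visual acuity". Surgeon is the randomisation stratum (Assignment of interventions).
- **Cited harm.** The Background reports that in an earlier trial of 5-FU with LMWH, treatment of macula-on eyes "led to a significant reduction in the final postoperative visual acuity in comparison with control patients" (P = 0.0091), while overall acuity did not differ significantly (P = 0.072). Table 1 shows the same concentrations as here, 200 μg/mL and 5 IU/mL.
- **Eligibility.** Macula-on detachment is not an exclusion criterion.
- **Safety measure.** Adverse events and safety reporting defines an adverse event of special interest (AESI) for eyes with "primary rhegmatogenous retinal detachment with macula-on status prior to surgery". It is handled as an SAE, and Statistical methods provides for comparing SAE rates between arms by treatment received.

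**The concern.** Acuity is the outcome on which the protocol reports previous harm from this drug combination, and it locates the significant result in one kind of eye. The stated BCVA summary pools that kind with all others and ignores preoperative acuity, although that is measured.

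Two things are lost. The first is precision, because baseline acuity and surgeon are prognostic information that the summary leaves unused. The protocol itself says that the surgeon considerably influenced surgical outcome in a previous study. The second is visibility: an effect confined to macula-on eyes is diluted in the pooled arm summaries. The primary endpoint, by contrast, gets relative and absolute risk differences with confidence intervals, overall and within surgeon strata. For BCVA no estimated difference is stated at all. At stake is whether the trial can say anything quantitative about the visual cost of a treatment that might reduce PVR.

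**Working it through.** **Plan's own figures.** The protocol gives no calculation for BCVA. The only usable input is the group size, which reproduces:
- 35% versus 23.33%, two-sided 5%, 80% power: 237.09 per arm by the pooled-variance formula.
- Times the two-look O'Brien-Fleming inflation factor 1.00779: 238.9, so 239 per arm and 478 in total, as stated.
- 478/0.95 = 503.2 (stated 504); 504/0.95² = 558.4 (stated 560, or 280 per arm).

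The sample size is not in dispute.

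**Inputs that must be assumed.** The documents give none of these: baseline to follow-up correlation r (0.3, 0.5, 0.7); macula-on share q (10% to 50%); a harm of 0.3 SD confined to macula-on eyes. All 280 per arm are taken to have BCVA unless stated otherwise.

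**1. Gain from baseline adjustment.** Residual variance factor = 1 − r². Difference detectable with 80% power = 2.80 × √(2(1 − r²)/n), in SD units, where 2.80 = 1.96 + 0.84.

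| r | Variance factor | n = 280 per arm | n = 252 per arm |
|---|---|---|---|
| 0 (unadjusted) | 1.00 | 0.237 | 0.250 |
| 0.3 | 0.91 | 0.226 | 0.238 |
| 0.5 | 0.75 | 0.205 | 0.216 |
| 0.7 | 0.51 | 0.169 | 0.178 |

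Here 252 = 504/2, the size per arm before the dropout allowance. Variance falls by 9% to 49%.

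**2. Dilution by pooling.** If the effect exists only in macula-on eyes, pooled difference = q × effect. Power here is the chance of a significant result in the direction of harm, unadjusted, at two-sided 5%.

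| q | Macula-on per arm (280q) | Pooled difference (0.3q), SD | Power, pooled | Power, macula-on only | 95% CI half-width, macula-on (1.96 × √(2/(280q))), SD |
|---|---|---|---|---|---|
| 10% | 28 | 0.03 | 5% | 20% | 0.52 |
| 30% | 84 | 0.09 | 19% | 49% | 0.30 |
| 50% | 140 | 0.15 | 43% | 71% | 0.23 |

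Baseline adjustment sharpens the pooled estimate but does not undo the dilution. Only the split does that.

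**3. Precision of the interaction.** Standard error = √(2/(280q) + 2/(280(1 − q))): 0.282 SD at q = 10% and 0.169 SD at q = 50%. A 0.3 SD interaction is then between 0.3/0.282 = 1.1 and 0.3/0.169 = 1.8 standard errors, so the interaction can be estimated but not reliably detected.

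**4. What the AESI captures.** It is triggered when acuity fails to recover to 0.3 logMAR or better, or falls beyond 0.3 logMAR, and only if no structural cause is found. A macula-on eye that drops from 0.0 to 0.3 logMAR does not cross the limit. Loss with a structural finding is not counted either. SAE rates are stated for the safety population, which is all operated patients; no macula-on denominator is given. With share q, an AESI rate over all eyes is q times the rate over the eyes that can have the event.

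**The case against.** The strongest reply is that the sponsor did respond to the cited signal. A reader might infer that macula-on visual loss is reviewed only case by case, with no comparison between arms. The documents do not support that: the AESI is an SAE, SAE rates are compared between arms, and an external DMC reviews safety every six months. This stands. It does not supply an estimated acuity difference, for the reasons in step 4 of the working.

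Second, a reader might infer that only raw means are reported. That is also too strong: SD, median, quartiles and range are listed, and P values are allowed.

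Third, covariates and subgroup tables for a non-confirmatory endpoint often sit in a statistical analysis plan, which is not shown. Silence alone would be no finding. But the article does more than stay silent: it names descriptive methods, the groupings and the aggregation for BCVA, and an analysis plan consistent with that text would produce unadjusted arm summaries.

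Fourth, a reader might infer that the earlier harm occurred only in macula-on eyes, or that opposite effects in the two kinds of eye could cancel. The article gives no macula-off result and reports no visual benefit in such eyes. An overall P of 0.072 does not show that the other eyes were unharmed. The dilution figures are therefore a scenario, not a reading of the earlier trial.

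Finally, omitting baseline does not bias a randomised comparison, and secondary results are declared non-confirmatory. Both points are right. They limit the matter to precision and visibility.

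**Conclusion.** The point holds as a better method than the one stated, available at almost no cost. It is not an error that threatens the primary analysis. The protocol fixes unadjusted descriptive summaries by arm for the endpoint on which it cites prior harm, in a population that includes the eyes concerned.

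The size can be given only as a range. Adjustment removes 9% to 49% of residual variance for an assumed correlation of 0.3 to 0.7. Pooling leaves 10% to 50% of a macula-on-only effect for an assumed share of 10% to 50%.

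The split is no guarantee of detection. For an assumed harm of 0.3 SD, power in macula-on eyes is about 20% to 71%, and the interval is wide if few such eyes are enrolled. Adjustment would help there too, but the correlation within one stratum may be lower than the overall one, because part of the overall correlation may reflect the contrast between macula-on and macula-off eyes. The value of the stratum result is an honest estimate with its uncertainty, not a test.

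**What to change.** State the following in the statistical analysis plan, all as exploratory:

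1. Estimate the difference in BCVA between arms at 6 and at 12 weeks, with 95% CI, by ANCOVA with preoperative BCVA and surgeon as covariates. Keep the descriptive summaries alongside.
2. Add macula status (on/off) and its interaction with treatment. Report the treatment difference with 95% CI separately in macula-on and macula-off eyes, and the interaction with its CI. Fit this as one model on all eyes, so that surgeon effects are not estimated from the stratum alone. At a 10% share, 56 macula-on eyes over the 24 surgeons assumed in the sample size section would be about 2.3 each.
3. Report AESI counts by arm with macula-on eyes as the denominator, in addition to the SAE comparison already planned.

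The cost is wording and programming. Preoperative ETDRS acuity and surgeon are already recorded, and the AESI cannot be applied without macula status. The sponsor should confirm that macula status is held as a data field for every patient, not only for those with an event. Sample size, alpha and the primary analysis are unchanged.
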